#### 2D transthoracic echocardiography

2.6.2

Transthoracic echocardiographic (TTE) assessment will be performed at first and last follow-up visit in all patients. Evaluation of cardiac diameters and volumes, systolic and diastolic performance of LV, speckle tracking, and Dobutamine viability test will be conducted with a Vivid E9 ultrasound system (General Electric Vingmed Ultrasound, Horten, Norway), with the patient turned slightly on his left side, according to American College of Echocardiography indications. Left ventricular end-systolic volume (LVESV), left ventricular end-diastolic volume (LVEDV), and left ventricle ejection fraction (LVEF) will be evaluated using the Simpson's method, on the basis of images obtained from apical four chamber view. All measurements will be calculated as an average from 3 heart cycles.

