#### Late gadolinium-enhancement cardiac magnetic resonance (LGE-CMR)

2.6.3

All cardiac magnetic resonance images will be acquired with the use of a 1.5T Siemens Magnetom Aera equipment. The structure and function of the LV will be assessed by cine acquisitions in the long axis, 2-chamber and 4-chamber view respectively, as well as short axis, from the mitral plain through the apex. Short axis cine images will also be used for assessment of LV mass, LVEF, end-diastolic and end-systolic volumes of the LV. The LGE-CMR will be used to evaluate the myocardial scar, degree of fibrosis and the remodeling process of the LV. The images will be acquired during the diastolic phase of the cardiac cycle, by using the same views as for cine imaging, respectively short and long axis views, but after a 10 minutes delay after gadolinium intravenous injection. Imaging data post-processing will be conducted with the use of Medis Q Mass 8.1 software (Medis, Leiden, the Netherlands), by manually tracing the epicardium and endocardium. The analysis of the delayed signal intensity (DSI) will be conducted in 10 to 12 successive short-axis LGE slices. Image segmentation will use an automated hyper-enhancement threshold, and myocardial regions with a slow washout kinetic will be considered as fibrotic areas. The volume of the epicardial adipose tissue will be measured by a semiautomatic protocol for image post-processing, using automatic tracing and manual adjustments for epicardial layers.

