### Outcomes

2.8

The *primary outcome* of the study refers to the incidence of post-infarction heart failure development, defined as the rate of re-admission in the hospital for heart failure or by a significant decrease in the ejection fraction (<45%).

*Secondary outcomes* of the study are represented by rate of re-hospitalization rates, rate of repeated revascularization and major adverse events (MACE) rates, including cardiovascular death or stroke.

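### Echo LVEF and volumes come from the apical four-chamber view alone, so the EF <45% part of the primary outcome is liable to error that depends on infarct territory

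*Protocol article*

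**What the plan says.** All references are to the protocol article.

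- **Echo method (2.6.2).** LVESV, LVEDV and LVEF are obtained by Simpson's method "on the basis of images obtained from apical four chamber view". The same section adds: "All measurements will be calculated as an average from 3 heart cycles".
- **Primary outcome (2.8).** Post-infarction heart failure is "defined as the rate of re-admission in the hospital for heart failure" or "by a significant decrease in the ejection fraction (<45" per cent). No modality is named for the EF limb.
- **CMR (2.6.3).** "Short axis cine images will also be used for assessment of LV mass, LVEF, end-diastolic and end-systolic volumes of the LV". Long-axis 2-chamber and 4-chamber cines are also acquired.
- **Schedule (2.9).** LGE-CMR is listed at month 1 only. At months 3, 6 and 9, and at the month-12 visit where end-points are assessed, the only cardiac imaging listed is 2D TTE.
- **Population (2.3.1, 2.3.2).** STEMI treated by primary PCI within 12 hours, with no restriction on infarct location.

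**The concern.** Biplane Simpson needs two apical views. Naming one view specifies the single-plane version, which assumes that the rest of the ventricle behaves like the plane that was imaged. The four-chamber plane shows the septal and lateral walls; the anterior and inferior walls lie outside it. After STEMI that assumption is least safe. If the akinetic wall is out of plane, EF tends to be read too high; if it is in plane and the unseen walls contract well, EF tends to be read too low.

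Two things rest on this measurement: whether a patient counts as a primary-outcome event through EF <45%, and the serial echo volumes that describe remodeling after month 1. In a study of 100 patients, avoidable error at a fixed cut-off costs information, and the missing view cannot be recovered later if it was not recorded.

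**Working it through.** **Step 1: which EF feeds the outcome?** Section 2.8 does not say, so the schedule has to decide.

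| Time | Cardiac imaging listed in 2.9 | Can it supply LVEF? |
|---|---|---|
| Baseline | 2D TTE, speckle tracking | Yes, four-chamber only |
| Month 1 | Angio-CT, LGE-CMR, dobutamine echo with speckle tracking | Yes, CMR short-axis cines |
| Months 3, 6, 9 | 2D TTE | Yes, four-chamber only |
| Month 12, end-point assessment | 2D TTE | Yes, four-chamber only |

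From month 3 onward, EF can only come from the single-plane echo. This is an inference from the schedule, but no other source is listed.

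Section 2.6.2 places TTE at the first and last follow-up visits, whereas 2.9.4 also lists it at months 3, 6 and 9. These need reconciling so that it is clear which EF readings count. The point holds on either reading, because month 12 is TTE on both.

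**Step 2: is there a figure in the plan to reproduce?** No. The documents give no echo error, EF distribution or expected rate of EF <45%. The sample size in 2.10 (50 per group, 90% power) is built on major adverse events, not on this outcome, and is used here only for n = 50 per group.

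**Step 3: illustration of what EF error costs.** Assumptions, none from the documents except the 45% cut-off, n = 50 per group and two-sided alpha 0.05:

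- true EF normal with SD 8 in each group;
- true rates of EF <45% of 40% and 15%;
- normal measurement error with mean 0 and SD *e*, the same in both groups;
- the EF component taken alone; equal groups; exact power of the Pearson chi-square test.

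Group means follow from mean = 45 − 8·z(rate):

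- 40%: 45 + 8 × 0.253 = 47.0
- 15%: 45 + 8 × 1.036 = 53.3

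Observed SD = √(8² + *e*²), and observed rate = Φ((45 − mean)/observed SD).

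| Total error SD *e* | Observed SD | Observed rates | Difference | Power |
|---|---|---|---|---|
| 0 | 8.0 | 40.0% vs 15.0% | 25.0 points | 82% |
| 4 | 8.9 | 41.0% vs 17.7% | 23.3 points | 74% |
| 6 | 10.0 | 42.0% vs 20.4% | 21.6 points | 65% |
| 8 | 11.3 | 42.9% vs 23.2% | 19.7 points | 56% |

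The first row is not what a better method delivers, because biplane echo also has error. The gain is the difference between two rows. If single-plane had SD 6 and biplane SD 4, power would go from 65% to 74%, a gain of 9 points.

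**Step 4: direction.** Step 3 adds random error only. With true EF assumed normal (mean 50, SD 10) and error SD 3 to 9:

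| Systematic bias | Sensitivity for EF <45% | Specificity |
|---|---|---|
| None | 73–88% | 81–94% |
| +3 points | 62–69% | 88–99% |
| −3 points | 82–97% | 73–82% |

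Bias in opposite directions produces opposite kinds of error. Which one dominates depends on the mix of territories, which the documents do not give.

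**The case against.** The strongest objections, and what stands of each:

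- **The article is condensed, and an echo manual may specify more.** This carries some weight. However, the sentence does not omit the view; it names one. A correction to that sentence is fair.
- **There are mitigations.** Averaging three cycles reduces beat-to-beat noise but adds no second plane. Speckle tracking is planned but is not given as the source of LVEF. CMR covers all walls and supports the viability and remodeling objective at month 1. It limits the consequence but does not supply an end-point EF.
- **Re-admission for heart failure is untouched.** This stands. A reader might treat EF <45% as half of the primary outcome, but no such share is documented, and the power figures above apply to the EF limb alone.
- **The effect on the group comparison is unknown.** This stands. A reader might infer that the outcome *is* misclassified and the group difference necessarily diluted. The documents support only *liable to be*. Dilution follows if the error is unrelated to hs-CRP group; if territory is related to group, the distortion could go either way.

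A larger power loss is also tempting. Deriving one sensitivity/specificity pair from a single population (mean EF 52, SD 8) and applying it to both groups gives 52%, 38% and 29% at error SD 4, 6 and 8. Those figures should not be used. Under a normal model, sensitivity and specificity at a cut-off change with each group's EF distribution, and the consistent calculation gives 74%, 65% and 56%.

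**Conclusion.** The point holds as a measurement weakness that is cheap to remove. The protocol fixes echo LVEF and volumes to one plane in a population with regional injury, and the schedule leaves that echo as the only listed source of EF from month 3 through the end-point visit. The EF <45% component and the serial echo volumes are therefore liable to territory-dependent error.

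Neither the size nor the direction can be derived from the documents. On the stated assumptions, moving from total error SD 6 to SD 4 is worth about 9 points of power on the EF component alone. The effect on the full primary outcome would differ, because re-admission does not depend on the echo view. This is a change that should be made; it does not invalidate the study.

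**What to change.** - In 2.6.2, specify that LVEDV, LVESV and LVEF are measured by biplane Simpson, from the apical four- and two-chamber views, at every scheduled TTE.
- In 2.8, state that this biplane TTE LVEF decides EF <45%.
- Reconcile the TTE visits in 2.6.2 with those in 2.9.4, so that the readings that count are unambiguous.

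Cost: one more standard view and tracing, a few minutes per echo. No extra visit, procedure or staff is needed.

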#### Late gadolinium-enhancement cardiac magnetic resonance (LGE-CMR)

2.6.3

All cardiac magnetic resonance images will be acquired with the use of a 1.5T Siemens Magnetom Aera equipment. The structure and function of the LV will be assessed by cine acquisitions in the long axis, 2-chamber and 4-chamber view respectively, as well as short axis, from the mitral plain through the apex. Short axis cine images will also be used for assessment of LV mass, LVEF, end-diastolic and end-systolic volumes of the LV. The LGE-CMR will be used to evaluate the myocardial scar, degree of fibrosis and the remodeling process of the LV. The images will be acquired during the diastolic phase of the cardiac cycle, by using the same views as for cine imaging, respectively short and long axis views, but after a 10 minutes delay after gadolinium intravenous injection. Imaging data post-processing will be conducted with the use of Medis Q Mass 8.1 software (Medis, Leiden, the Netherlands), by manually tracing the epicardium and endocardium. The analysis of the delayed signal intensity (DSI) will be conducted in 10 to 12 successive short-axis LGE slices. Image segmentation will use an automated hyper-enhancement threshold, and myocardial regions with a slow washout kinetic will be considered as fibrotic areas. The volume of the epicardial adipose tissue will be measured by a semiautomatic protocol for image post-processing, using automatic tracing and manual adjustments for epicardial layers.

#### Coronary computed tomographic angiography

2.6.4

Coronary Computed Tomographic Angiography associated with complex post-processing will be used for assessment of pan-coronary plaque vulnerability (based on vulnerability features: positive remodeling, spotty calcification, napkin-ring sign, low-density plaque), myocardial perfusion and for quantification of epicardial fat volume, using a 128-slices dual-source computer tomography (CT) scanner (SOMATON Definition, Siemens Healthcare, Erlangen, Germany) and the work station Siemens Syngo Via Frontier – Coronary Plaque Analysis platform (Siemens Medical Solutions, Erlangen, Germany), available in the Laboratory of Advanced Research in Cardiac Multimodal Imaging of the Cardio Med Medical Center, Targu Mures, Romania.

### Study timeline

2.7

VIABILITY study will be conducted from March 2019 to March 2021.

### Outcomes

2.8

The *primary outcome* of the study refers to the incidence of post-infarction heart failure development, defined as the rate of re-admission in the hospital for heart failure or by a significant decrease in the ejection fraction (<45%).

*Secondary outcomes* of the study are represented by rate of re-hospitalization rates, rate of repeated revascularization and major adverse events (MACE) rates, including cardiovascular death or stroke.

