### Sample size

2.10

One hundred patients with STEMI who underwent successful revascularization of the culprit lesion within the first 12 hours after the onset of symptoms will be enrolled in this study. On the basis of the persistence of systemic inflammation at 7 days after the acute event patients will be allocated into 2 subgroups. Stat Mate 2.0 software was used in order to establish the sample size of the study. According to this computation, a sample size of 50 subjects per group presents a 90% power to detect an increase in major adverse CV events rates proportion of 3.28, with a significance level (alpha) of 0.05 (2-tailed). Therefore, the study population was established at 100 subjects.

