### Statistical analysis

2.11

Graph Pad in Stat 3.10 software (GraphPad Software, San Diego, CA) will be used in order to perform all the statistical analysis, using a level of significance of 5%. Normality tests will be performed in order to check all study data. Categorical variables will be interpreted with Pearson Chi-Square test and being presented as numerical or percentage values respectively. Continuous variables will be presented in the form of a mean value +/- SD and will be compared using the Student test for variables with gaussian distribution and Mann–Whitney test for variable with non-gaussian distribution.

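### Continuous LVEF enters the primary composite only as a cut at 45%, and the only stated test of LVEF itself ignores the day-0 reading; a baseline-adjusted or ranked analysis would use the data better

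*Protocol article*

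**What the plan says.** Section 2.8 (Outcomes) makes the primary outcome an incidence of heart failure, "defined as the rate of re-admission in the hospital for heart failure or by a significant decrease in the ejection fraction (<45"%). Each patient either has the event or does not, through re-admission or through LVEF below the cut.

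Section 2.6.2 states that "left ventricle ejection fraction (LVEF) will be evaluated using the Simpson's method", averaged over three heart cycles, so the raw measurement is continuous. The visit schedule lists transthoracic echocardiography at day 0 (2.9.1), months 3, 6 and 9 (2.9.4) and month 12 (2.9.5). Section 2.6.2 itself places it only at the first and last follow-up visits.

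Section 2.11 gives the tests. "Categorical variables will be interpreted with Pearson Chi-Square test" covers the primary outcome. For LVEF as a measurement, "Continuous variables will be presented in the form of a mean value +/- SD and will be compared using the Student test", with Mann–Whitney if the distribution is not Gaussian. No model with a baseline covariate is named.

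Section 2.10 states that "a sample size of 50 subjects per group presents a 90% power", for a two-sided test at the 5% level. The effect behind this figure is printed as 3.28, on a scale that is not given. That calculation concerns major adverse events, a secondary outcome in 2.8. No power is given for the primary outcome.

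**The concern.** A cut turns a graded measurement into one bit. Two patients far apart on the same side of 45% count the same, and two patients close together on opposite sides count as different. In a cohort of 100 this can hide a moderate difference in LV function between the two hs-CRP groups. The loss is avoidable, because the readings needed to show the difference are already scheduled.

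The stated alternative does not fully recover the information. A Student or Mann–Whitney comparison of LVEF uses the scale but not the day-0 value of the same patient. Nor does 2.8 give continuous LVEF any status as an outcome, so a finding on it would have no declared standing beside a non-significant chi-square test.

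**Working it through.** **The plan's own figure.** The stated 50 per group and 90% power cannot be confirmed, because no control-group rate is printed and the scale of 3.28 is not given. Read as a rate ratio, it gives 90% at 50 per group only if the rates are about 12.2% and 40.2% (0.122 × 3.28 ≈ 0.40). At a 10% control rate, power is 80%. In any case it refers to major adverse events, so it says nothing about power for the primary outcome.

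**Inputs for the check.** From section 2.10: 50 per group, two-sided 0.05. From section 2.8: the cut at 45%. Assumed, because the article does not give them: normal LVEF with equal SD in both groups, a proportion p0 of the reference group below 45%, and a shift of d SD in the other group.

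**LVEF limb alone, p0 = 0.15, d = 0.5** (5 EF points if the SD is 10):

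- Proportion below the cut in the shifted group: p1 = Φ(Φ⁻¹(0.15) + 0.5) = Φ(−1.036 + 0.5) = 0.296.
- Chi-square: pooled proportion 0.223; null SE = √(0.223 × 0.777 × 2/50) = 0.0832; alternative SE = √((0.15 × 0.85 + 0.296 × 0.704)/50) = 0.0820. Power = Φ((0.146 − 1.96 × 0.0832)/0.0820) = Φ(−0.21) = 0.42.
- Student test on LVEF: noncentrality 0.5 × √25 = 2.5 on 98 df; power 0.70.
- With day-0 LVEF as covariate and an assumed correlation r = 0.5: effective shift 0.5/√(1 − 0.25) = 0.577; power about 0.82.

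At d = 0.6 the three figures are 57%, 84% and 93%.

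**Range of the loss, Student test against the cut, LVEF limb:**

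| Shift (SD) | Points lost, p0 from 0.10 to 0.30 |
|---|---|
| 0.2 | 5–8 |
| 0.3 | 11–17 |
| 0.4–0.7 | about 15–35 |
| 0.9 | 5–13 |

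A second parameterisation agrees (SD 8–12, reference mean 45–55, difference 3–8 points). The loss is 15–34 points, median 21, where the continuous test has 70–95% power. Over the whole grid it is 2–34, and 37% of scenarios lose less than 15.

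**The full composite.** Add a re-admission limb with probability r, independent of LVEF, so that the event rate is 1 − (1 − p)(1 − r). Keep p0 = 0.15, d = 0.5, with 5% re-admission in the reference group: 1 − 0.85 × 0.95 = 0.1925.

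| Re-admission, reference vs other | Power, composite by chi-square | Power, LVEF by Student test |
|---|---|---|
| 5% vs 5% | 35% | 70% |
| 5% vs 10% | 49% | 70% |
| 5% vs 15% | 63% | 70% |
| 5% vs 20% | 76% | 70% |

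The composite goes from 35 points behind to 6 points ahead.

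**Ranked composite.** Rank re-admission worse than any LVEF value, order the rest by LVEF, and apply Mann–Whitney. Simulation (4,000 runs per scenario, 50 per group, SD 10, re-admission independent of LVEF) gave these powers, chi-square on the composite against the ranked test:

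- mean 55, difference 5, re-admission 5% vs 10%: 50% against 70%
- mean 55, difference 5, re-admission 5% vs 20%: 76% against 89%
- mean 50, difference 6, re-admission 5% vs 20%: 86% against 95%

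Over 16 equal-split scenarios the gain was about 9 to 23 points, with type I error 5.0% for both tests. With a 70/30 split (mean 55, difference 5, 5% vs 10%) it was 46% against 63%. These runs contain no deaths.

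**The case against.** The strongest reply is that the outcome is a clinical composite and not a dichotomised LVEF. Heart-failure re-admission matters to patients in its own right. The introduction names several routes from infarction and inflammation to heart failure, so re-admission need not follow LVEF. If it differs strongly between groups, the composite can beat LVEF alone, as the last row of the composite table shows. Replacing heart-failure incidence by mean LVEF would also change the clinical question. All of this stands, and it is why the composite should be kept.

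A reader might infer that the trial simply loses 15 to 35 points of power on its primary outcome. The article does not support that. The range belongs to one limb, at moderate effects, under an LVEF distribution that the article does not state. If 3.28 is read as a ratio and applied to that limb (12.2% vs 40.2%, d = 0.91), the binary test has 90% and the Student test over 99%, a loss of only 9 points.

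A reader might also infer that LVEF will never be analysed on its own scale. Section 2.11 does allow it. What is missing is the adjustment for day 0 and a declared place among the outcomes. The absence of a source for 45% proves little either, since a journal article condenses the full protocol.

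The covariate gain has its own weakness. The correlation of 0.5 is assumed, and the day-0 reading is taken in the acute phase, when section 1.1 describes stunning. The formula also supposes equal mean day-0 LVEF in groups that are not randomised. The gain is therefore illustrative.

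**Conclusion.** The point holds in a limited form. The plan puts a continuous measurement into its primary outcome only through a cut, tests the result by chi-square, and offers only an unadjusted comparison for the measurement itself. On the LVEF limb the cut costs about 15 to 35 points of power for shifts of 0.4 to 0.7 SD, and about 5 to 17 points at 0.2 to 0.3 SD or 5 to 13 at 0.9 SD. This assumes normal LVEF, equal SD, 50 per group and 10–30% of the reference group below 45%. For the composite as a whole no single figure can be given: against LVEF alone it runs from a loss of about 35 points to a gain of about 6. A ranking that keeps re-admission did better than chi-square on the composite in every equal-split scenario simulated.

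This does not invalidate the outcome. It is an avoidable loss of information in a small cohort for which no power on the primary outcome is shown, and it is worth correcting. Confidence in the direction is good; confidence in the size is moderate, because every LVEF input is assumed.

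**What to change.** Keep heart-failure incidence as the clinical outcome in 2.8. In 2.8 and 2.11, name month-12 LVEF on its continuous scale as a key analysis of LV function: a linear model on hs-CRP group with day-0 LVEF as covariate, reported as a difference in EF points with a 95% confidence interval. State how patients without a month-12 reading, including those who die, are handled.

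Alternatively, if one composite is preferred, rank patients with death worst, then heart-failure re-admission, then the remainder by month-12 LVEF. Compare groups by Mann–Whitney, which 2.11 already names. This gives death an explicit place.

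In either case, reconcile the echocardiography timing in 2.6.2 with 2.9.1, 2.9.4 and 2.9.5, since the adjusted analysis needs a day-0 reading in every patient.

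The cost is wording in two sections and one model, with no added patients, visits or measurements. The covariate model may need software other than the package named in 2.11; the ranked option does not. The downside is that a rank result or a mean difference in EF is less directly clinical than an event rate, so the composite and re-admission rates should still be reported beside it.
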